## Abstract

**Background:**

Atopic dermatitis (AD) is a chronic inflammatory skin disease that affects 10 to 20% of children and between 2 and 15% of the adults in Western Europe. Since 2000, therapeutic clothing or functional textiles based on silver or chitosan as antibacterial agents were introduced for AD. These agents aim to reduce skin colonization with *Staphylococcus* (*S*.) *aureus*. Increased colonization with *S. aureus* is correlated with increased AD severity. The antimicrobial effects of silver and chitosan have been demonstrated before. At this point, there is insufficient evidence for the effectiveness of antibacterial therapeutic clothing in patients with AD.

**Methods:**

This is a pragmatic randomized controlled double-blind multi-center trial comparing the effectiveness of antibacterial therapeutic clothing based on silver or chitosan as compared with non-antibacterial therapeutic clothing in patients with moderate to severe AD. A total of 165 participants, aged 0 to 80, diagnosed with moderate to severe AD are included. The study is performed in the Erasmus MC University Medical Center, University Medical Center Groningen, University Medical Center Utrecht, Amsterdam University Medical Centers, and St. Antonius Hospital Nieuwegein. Patients will be randomized 1:1:1 into one of the three intervention groups: group A will receive therapeutic clothing without antimicrobial agents, group B will receive microbial growth reducing therapeutic clothing based on chitosan, and group C will receive antimicrobial clothing based on silver. All therapeutic clothing is to be worn at night during the 12-month intervention period. Usual care is continued. The primary objective is to assess the effectiveness of antibacterial clothing (silver and chitosan group) as compared to non-antibacterial clothing assessed with the Eczema Area and Severity Index at 12 months compared to baseline. Secondary outcomes include between-group differences in physician- and patient-reported outcome measures, topical therapy use, *S. aureus* skin colonization, and safety. Data will be collected at baseline and after 1 month, 3 months, 6 months, and 12 months. A cost-effectiveness analysis will be performed.

**Discussion:**

This trial will provide data on the effectiveness, cost-effectiveness, and safety of antibacterial therapeutic clothing for patients with AD.

**Trial registration:**

ClinicalTrials.gov NCT04297215. Registered on 5 March 2020

**Supplementary Information:**

The online version contains supplementary material available at 10.1186/s13063-021-05836-y.

## Background

Atopic dermatitis (AD) is a chronic inflammatory skin disease that affects 10 to 20% of children in Western Europe [1]. About 70% of childhood AD will disappear spontaneously before adolescence and can be considered transient [2]. The prevalence among adults is estimated between 2 and 15%. Most patients are diagnosed with mild AD and are treated by a general practitioner. AD severity scores in Dutch general practices indicate that over 70% of pediatric patients have mild AD, while 28% have moderate and 2% severe disease [3].

AD treatment is aimed at control of inflammation, repair of the disrupted skin barrier with hydrating topical treatment, and avoidance of provoking factors. Anti-inflammatory drugs like corticosteroid creams and ointments are used to control inflammation. Emollients are used to improve hydration of the dry skin. Furthermore, therapeutic clothing has been used for decades as part of AD treatment. Historically, cotton bandages were used to cover the affected skin. This provides a fixation of creams and ointments, thereby possibly enhancing their action. It also protects the skin from further damage through scratching and irritating factors [4]. In the year 2000, therapeutic clothing or functional textiles based on silver or chitosan as antibacterial agents were introduced. The antibacterial properties of silver [5] and chitosan [6] have been demonstrated in healthcare before. In atopic dermatitis, antibacterial therapeutic clothing aims to reduce skin colonization with *Staphylococcus* (*S*.) *aureus*. Increased colonization with *S. aureus* is correlated with increased AD severity, and *S. aureus* induces further dysregulation of the inflammatory process [7, 8].

The effectiveness of (antibacterial) therapeutic clothing has been evaluated in several studies. A systematic review by the Dutch Society of Dermatologists (NVDV) concluded that there was insufficient evidence for the effectiveness from literature based on heterogeneity in treatments of small studies [9, 10]. However, both patients and clinicians had a positive experience with the use of antibacterial therapeutic clothing for the treatment of atopic dermatitis. Therefore, in the Dutch treatment guideline for AD, therapeutic clothing is advised in patients with moderate to severe dermatitis in whom a large surface area (>30%) is affected and those who suffer from severe itch, while treatment with topical corticosteroids cannot be tapered off [10]. More recently, the Dutch National Health Care Institute performed a systematic search on the same subject [11] and included two more studies [12, 13]. They concluded that, using the GRADE method for quality of evidence, there is low-quality evidence for the (cost-)effectiveness of silver-coated therapeutic clothing on the long term (90 days) and very low-quality evidence for the effectiveness on the short term (14 days to 4 weeks). Based on this report, the Dutch National Health Care Institute underlined the need for a trial to establish whether or not antibacterial therapeutic clothing is (cost-)effective for AD.

In this randomized controlled trial, we aim to investigate the (cost-)effectiveness of antibacterial therapeutic clothing (based on silver or chitosan) as compared to therapeutic clothing without these agents on reducing AD severity, thereby providing high-quality evidence to inform clinical practice.

## Methods

### Design and setting

The ABC study (AntiBacterial Clothing study) is a pragmatic, multi-center, double-blind, randomized controlled trial. The study aims to investigate the effectiveness of antibacterial therapeutic clothing based on silver or chitosan as compared with non-antibacterial therapeutic clothing in patients with moderate to severe AD. The study will be performed at the department of dermatology of the Erasmus MC in close collaboration with the departments of dermatology of the University Medical Center Groningen, University Medical Center Utrecht, Amsterdam University Medical Centers, and St. Antonius Hospital Nieuwegein. Both enrollment and the follow-up visits will take place at these five locations.

### Ethical considerations

The study follows the Dutch Medical Research Involving Human Subjects Act 1998 (WMO), the principles of the Helsinki Declaration 2008, and the European GDPR. All study procedures have been approved by the Institutional Review Board of the Erasmus MC University Medical Centre Rotterdam, The Netherlands (reference 2018-1609). Protocol amendments will be submitted for review at the Institutional Review Board.

### Participants

The study population consists of patients of all ages with moderate to severe AD according to the criteria of Williams [14]. Participants are eligible with an Eczema Area and Severity Index (EASI) score ≥ 6 at baseline [15]. Patients are not eligible if treated with therapeutic clothing, oral antibiotics, systemic immunosuppressive agents, or UV therapy until 1 month before inclusion or if treated with topical antibiotics within 1 week before inclusion. Other exclusion criteria are anamnestically assessed kidney function impairment, pregnancy or pregnancy wish, hypersensitivity to silver, or evidence of past non-compliance to treatments or appointments.

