### Recruitment, inclusion, and consent

Patients are recruited from five hospitals across the country: Erasmus MC University Medical Center, University Medical Center Groningen, University Medical Center Utrecht, Amsterdam University Medical Centers, and St. Antonius Hospital. In addition, dermatologists in the Netherlands are informed about the study through the Dutch Society of Dermatology and Venereology, the Dutch Trial Network, and through scientific conferences. The patient support group (Vereniging voor Mensen met Constitutioneel Eczeem) will inform their members on this study, and online media will be used to inform potential participants. In addition, online media will be used to inform potential participants. After receiving information, potential participants can contact each site for additional information and assessment of eligibility. Eligibility is checked by a member of the research team and AD expert. These recruitment methods will enable us to recruit a representative sample of patients with moderate to severe AD across the Netherlands. Patients who are willing to participate and fulfill the inclusion criteria will be included in the study after providing written informed consent.

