### Sample size

The null hypothesis of this study is that there is no difference between the antimicrobial therapeutic clothing (based on silver and chitosan) and therapeutic clothing without antimicrobial agents.

We used a standard deviation (*SD*) of 13 (based on the CLOTHES study [16]) and used the 6.6 minimal clinical important difference (MCID) for EASI as proposed by Schram et al. [17] resulting in an expected 0.51 Cohen’s *D* effect size. An alpha of 0.05 and a power of 0.80 were used.

Based on the inclusion of 3 groups, 5 measurements (baseline, 1 month, 3 months, 6 months, 12 months) and a 0.6 correlation between EASI scores (correlation is based on the CLOTHES study), while assuming a 20% loss to follow-up, we will include 55 patients per group and 165 patients in total.

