### Intervention

Patients will be randomized into one of three intervention groups. Group A will receive therapeutic clothing without antimicrobial agents (control group), group B will receive microbial growth reducing therapeutic clothing based on chitosan, and group C will receive antimicrobial clothing based on silver.

The therapeutic clothing is to be worn at least at night during a 12-month intervention period. Participants will be encouraged to wear the clothing during each visit.

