#### Therapeutic clothing

The control group will receive Binamed® therapeutic clothing without antimicrobial agents (BAP Medical). This is therapeutic clothing made of micro-modal and lycra. Micro-modal is a semi-synthetic wood cellulose fiber. This fiber has a high strength and elasticity and high moisture permeability.

The intervention groups receive either DermaCura® antimicrobial clothing (D&M) (group B) or Binamed antimicrobial therapeutic clothing (BAP Medical) (group C). DermaCura® antimicrobial clothing (D&M) is made from 98% TENCEL® C and 2% elastane. Chitosan (1%) is added to TENCEL ® C. Binamed antimicrobial therapeutic clothing (BAP Medical) consists of micro-modal lycra and woven silver filaments.

Patients will receive three sets of therapeutic clothing at the beginning of the study. During the study, three additional sets of therapeutic clothing can be requested by patients. Each set consists of a shirt with long sleeves and trousers. Socks and gloves can be prescribed if necessary. During the study, usual care (including the application of emollients, topical corticosteroid ointments, or creams only if needed and/or antihistamines) is continued according to the treatment guidelines of AD [10]. When AD worsens, the frequency and class of topical steroid treatment can be increased (as is usual care in the Netherlands). In case of a severe exacerbation requiring UV therapy or systemic treatment with immunosuppressive medication, participation in the study is stopped.

Measurements and assessments will be performed at baseline (start of intervention) and 1, 3, 6, and 12 months after baseline, as this reflects clinical practice. In addition, participants are requested to answer a weekly questionnaire on the use of therapy, AD symptoms, and costs. See Additional file 1 for an overview of the Standard Protocol Items: Recommendations for Interventional Trials (SPIRIT) 2013 checklist items. See Fig. 2 for the SPIRIT diagram of the trial procedures.

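### The only hypersensitivity exclusion is for silver, although every participant has a one-in-three chance of being allocated the chitosan garment

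*Protocol article*

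**What the plan says.** The Participants section of the protocol article lists specific exclusions. After recent treatments and impaired kidney function it gives "pregnancy or pregnancy wish, hypersensitivity to silver, or evidence of past non-compliance to treatments or appointments". No other hypersensitivity criterion appears in the article.

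The Methods part of the abstract fixes the allocation: "Patients will be randomized 1:1:1 into one of the three intervention groups". Under Intervention, "group B will receive microbial growth reducing therapeutic clothing based on chitosan", while group C receives silver clothing and group A clothing without an antimicrobial agent. The Therapeutic clothing section gives the composition of the group B fabric: "Chitosan (1%) is added to TENCEL ® C". On exposure, the Intervention section says "The therapeutic clothing is to be worn at least at night during a 12-month intervention period".

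The Recruitment, inclusion, and consent section adds a check by people but no further criterion: "Eligibility is checked by a member of the research team and AD expert".

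**The concern.** Allocation is unknown when eligibility is assessed, so the entry criteria have to make a patient suitable for each of the three garments. The protocol accepts hypersensitivity to a garment's active agent as a reason not to enrol, but names only one of its two active agents and does not say why. A site that follows the list exactly would enrol a patient who is known to react to chitosan.

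What is at stake is mainly an avoidable exposure of a participant whose sensitivity was already known. A lesser matter is that the trial sets out to report on the safety of both agents. Patients known to be sensitive to silver are removed before the silver arm is observed. Patients known to be sensitive to chitosan are not removed before the chitosan arm is observed.

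**Working it through.** **1. Exclusion list set against the garments.**

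| Group | Active agent (Intervention; Therapeutic clothing) | Hypersensitivity exclusion (Participants) |
|---|---|---|
| A | none | not applicable |
| B | chitosan, 1% | none stated |
| C | silver filaments | stated |

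The stretch fibre does not separate the arms: the Therapeutic clothing section lists lycra in the group A and group C garments and elastane in group B. The mismatch therefore concerns the active agents only.

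**2. Whether anything else in the article closes the gap.** Stratification (Randomization and blinding) uses severity and age only, so nothing steers a sensitive patient away from group B. Labels are removed, a third party mails the clothing, the garment type is kept out of the digital patient file, and the treating clinician cannot see the CRFs until the study ends. A clinician who knows of a chitosan sensitivity could not learn from these sources that the patient had been sent chitosan. Screening is therefore the natural place to catch the mismatch. The expert eligibility check might catch it, but no criterion tells the expert to look.

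**3. Chance of receiving the chitosan garment.** The Sample size section says "we will include 55 patients per group and 165 patients in total". The share of group B is 55/165 = 1/(1+1+1) = 0.333, which agrees with the stated ratio.

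The 55 itself is close to what the protocol's inputs give. With a difference of 6.6, SD 13, two-sided alpha 0.05 and power 0.80, n = 2 × (13 × 2.80/6.6)² ≈ 61 per group. Taking the mean of four or five measurements with correlation 0.6 multiplies this by 0.70 or 0.68, giving 43 or 42. Dividing by 0.8 for loss to follow-up gives 54 or 53. The present point does not depend on these figures.

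**4. How many patients.** The documents give no frequency. If a proportion p of those enrolled had known chitosan hypersensitivity, the expected number enrolled is 165p, and the expected number in group B is 165p/3 = 55p. The values of p below are assumptions without any basis in the documents:

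| p (assumed) | Enrolled, 165p | In group B, 55p |
|---|---|---|
| 0% | 0 | 0 |
| 0.5% | 0.8 | 0.3 |
| 2% | 3.3 | 1.1 |

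**5. Effect on the primary outcome.** As an illustration (assumption), suppose one group B patient worsens by 20 EASI points. The mean of 55 patients moves by 20/55 = 0.36 points. Against the planned difference of 6.6 that is 0.36/6.6 ≈ 5.5%.

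**The case against.** The strongest reply is that nothing in the article contradicts anything else. It gives eligibility in one short paragraph, and the full protocol, screening form or product information may deal with garment components. The silver criterion may also be deliberate. The article treats silver as the agent with a specific risk: it raises possible uptake through the skin and measures urinary silver in that group only. It reports no known hypersensitivity to chitosan. A patient who knows of a reaction is unlikely to wear the garment for a year, given consent, weekly questionnaires and adverse-event registration.

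Much of this stands. It limits the point to a gap in a stated list and leaves open that there is a reason for it. It does not remove the point, because the article does not skip eligibility. It lists exclusions down to a wish for pregnancy and names one active agent but not the other. Twelve months is the planned exposure, not a certain one.

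A reader might infer that the arms become unequal and that the EASI comparison is biased against chitosan. The documents do not support this. The criteria act before randomisation, so sensitive patients are spread by chance over all three arms. A reaction to the chitosan garment would be a real effect of that garment in a pragmatic trial, and one such patient barely moves the mean. Nor does it follow that the safety results of the two agents cannot be compared. At most, a few agent-specific reactions could be seen in group B whose counterparts in group C were screened out.

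**Conclusion.** The concern holds in a limited form. Applied exactly, the exclusion list admits a patient with known hypersensitivity to one of the two active agents and gives that patient a one-in-three chance of being allocated it under blinding. The size cannot be computed from the documents. It is 55p patients in group B for an unknown p, which may be close to zero.

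The conclusion rests on the list in the article being the one that sites apply, and on the sensitivity being known at screening, since a history question cannot detect unknown sensitisation. The reason to act is participant protection first and like-for-like adverse-event data second. The primary analysis is not affected in any material way.

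**What to change.** Reconcile the hypersensitivity criterion in the Participants section with the composition given under Therapeutic clothing. Either the history-based criterion applied to all participants before randomisation covers the active agents of both intervention garments, or the protocol states why silver alone is listed. The investigators decide the clinical wording. If the full protocol already covers chitosan, only the article's list needs correcting.

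The cost is one line of text, one question at screening, submission of the amendment to the review board, and possibly a few more screen failures. No sample size or analysis figure changes.

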### Recruitment, inclusion, and consent

Patients are recruited from five hospitals across the country: Erasmus MC University Medical Center, University Medical Center Groningen, University Medical Center Utrecht, Amsterdam University Medical Centers, and St. Antonius Hospital. In addition, dermatologists in the Netherlands are informed about the study through the Dutch Society of Dermatology and Venereology, the Dutch Trial Network, and through scientific conferences. The patient support group (Vereniging voor Mensen met Constitutioneel Eczeem) will inform their members on this study, and online media will be used to inform potential participants. In addition, online media will be used to inform potential participants. After receiving information, potential participants can contact each site for additional information and assessment of eligibility. Eligibility is checked by a member of the research team and AD expert. These recruitment methods will enable us to recruit a representative sample of patients with moderate to severe AD across the Netherlands. Patients who are willing to participate and fulfill the inclusion criteria will be included in the study after providing written informed consent.

### Sample size

The null hypothesis of this study is that there is no difference between the antimicrobial therapeutic clothing (based on silver and chitosan) and therapeutic clothing without antimicrobial agents.

We used a standard deviation (*SD*) of 13 (based on the CLOTHES study [16]) and used the 6.6 minimal clinical important difference (MCID) for EASI as proposed by Schram et al. [17] resulting in an expected 0.51 Cohen’s *D* effect size. An alpha of 0.05 and a power of 0.80 were used.

Based on the inclusion of 3 groups, 5 measurements (baseline, 1 month, 3 months, 6 months, 12 months) and a 0.6 correlation between EASI scores (correlation is based on the CLOTHES study), while assuming a 20% loss to follow-up, we will include 55 patients per group and 165 patients in total.

### Randomization and blinding

Randomization is carried out by the Erasmus MC University Medical Center. Included patients are stratified before randomization. Patients are stratified according to the severity in the strata “moderate dermatitis” (EASI 6.0–22.9) or “severe dermatitis” (EASI 23.0–72.0) [15] and according to age (0–5, 6–17, and >18 years). ALEA Clinical software will be used for randomization (random block size randomization, blocks of 3 and 6) [18]. An overview of the randomization procedure is provided in Fig. 1.

**Fig. 1 Fig1:**
[figure not shown]
Flowchart of the study design

All labels and brand names are removed from the therapeutic clothing (“unlabeled”). In addition, the clothing will be provided by mail by a third party to ensure blinding.

Blinded efficacy assessors are unaware of treatment allocation. Furthermore, the type of therapeutic clothing is not described in the digital patient file and the treating clinician has no access to the CRFs until study completion.

### Intervention

Patients will be randomized into one of three intervention groups. Group A will receive therapeutic clothing without antimicrobial agents (control group), group B will receive microbial growth reducing therapeutic clothing based on chitosan, and group C will receive antimicrobial clothing based on silver.

The therapeutic clothing is to be worn at least at night during a 12-month intervention period. Participants will be encouraged to wear the clothing during each visit.

#### Therapeutic clothing

The control group will receive Binamed® therapeutic clothing without antimicrobial agents (BAP Medical). This is therapeutic clothing made of micro-modal and lycra. Micro-modal is a semi-synthetic wood cellulose fiber. This fiber has a high strength and elasticity and high moisture permeability.

The intervention groups receive either DermaCura® antimicrobial clothing (D&M) (group B) or Binamed antimicrobial therapeutic clothing (BAP Medical) (group C). DermaCura® antimicrobial clothing (D&M) is made from 98% TENCEL® C and 2% elastane. Chitosan (1%) is added to TENCEL ® C. Binamed antimicrobial therapeutic clothing (BAP Medical) consists of micro-modal lycra and woven silver filaments.

Patients will receive three sets of therapeutic clothing at the beginning of the study. During the study, three additional sets of therapeutic clothing can be requested by patients. Each set consists of a shirt with long sleeves and trousers. Socks and gloves can be prescribed if necessary. During the study, usual care (including the application of emollients, topical corticosteroid ointments, or creams only if needed and/or antihistamines) is continued according to the treatment guidelines of AD [10]. When AD worsens, the frequency and class of topical steroid treatment can be increased (as is usual care in the Netherlands). In case of a severe exacerbation requiring UV therapy or systemic treatment with immunosuppressive medication, participation in the study is stopped.

Measurements and assessments will be performed at baseline (start of intervention) and 1, 3, 6, and 12 months after baseline, as this reflects clinical practice. In addition, participants are requested to answer a weekly questionnaire on the use of therapy, AD symptoms, and costs. See Additional file 1 for an overview of the Standard Protocol Items: Recommendations for Interventional Trials (SPIRIT) 2013 checklist items. See Fig. 2 for the SPIRIT diagram of the trial procedures.

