### Primary outcome

The primary endpoint in this study is the difference in disease severity measured by the EASI [15] between the clothing without antimicrobial agents (control group) and microbial growth reducing/antimicrobial clothing based on chitosan or silver (intervention groups) at 12 months compared with baseline.

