### Cost-effectiveness

The economic evaluation of the clothing without antimicrobial agents (control group) and microbial growth reducing/antimicrobial clothing based on chitosan or silver (intervention groups) will be calculated as the incremental cost-effectiveness ratio (ICER). The primary effect outcome measures will be the effectiveness of the therapeutic clothing assessed by using the EASI for the cost-effectiveness analysis (CEA) and quality-adjusted life years (QALY) for the cost-utility analysis (CUA). QALYs will be measured for a 1-year period, based on the Dutch tariff for the EQ-5D.

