### Data collection, monitoring, and data analysis

ALEA will be used as a data management system [18]. Patient confidentiality will be ensured by using identification numbers. In a final stage, data from both management systems will be extracted to a SPSS dataset. Data management will be performed by the investigator and monitored by an independent monitor as predefined in the monitoring plan.

The data analysis will be conducted according to the intention-to-treat principle. The primary hypothesis is tested by means of linear mixed model analysis. The linear mixed model will use EASI as a dependent variable, and inclusion EASI, group, time, and time*group as independent variables; in addition, the EASI at baseline will be used as an additional covariate. As the time period between the visit varies (*t* = 1, 3, 6, and 12 months), time is defined as a continuous variable, in which we calculate the number of months from baseline. A two-sided alpha of 0.05 is used. Secondary outcome parameters will also be analyzed with linear mixed models. No interim analysis is planned, due to the low risks of participating in this study. Data will be available upon request.

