## Discussion

The ABC study is a pragmatic randomized controlled multi-center trial that compares the effectiveness of antibacterial therapeutic clothing with non-antibacterial therapeutic clothing in patients with moderate to severe AD. This study will provide high-quality evidence to inform clinical practice whether or not antibacterial therapeutic clothing is effective for AD. In addition, the cost-effectiveness of antibacterial clothing will be evaluated.

This study will also provide useful insights in the treatment of AD during a longer period. Data concerning the use of topical corticosteroids, adherence to the clothing, and use of other therapy will be available for analysis. In addition, the fact that both children and adults will participate from five centers across the Netherlands will provide us with data that can be used to compare age differences and treatment differences across a semi-national level. In addition, this trial will be the first trial to monitor the safety of textiles with silver in patients with the abnormal skin barrier.

In conclusion, the ABC trial will assess the (cost-)effectiveness and safety of antibacterial therapeutic clothing with chitosan and silver over a treatment period of 12 months in patients with moderate to severe atopic dermatitis.

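### Ending study participation at UV or systemic rescue means that later EASI (including month 12), EQ-5D and cost data are never collected for patients who leave because their eczema worsened

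*Protocol article*

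**What the plan says.** The rule is in the protocol article under Therapeutic clothing: "In case of a severe exacerbation requiring UV therapy or systemic treatment with immunosuppressive medication, participation in the study is stopped". The sentence before it lets topical steroids be stepped up while the patient stays in, so the article separates escalation of treatment from exit.

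Four other statements bear on it:

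- Design and setting: the study "is a pragmatic, multi-center, double-blind, randomized controlled trial".
- Primary outcome: control clothing is compared with "microbial growth reducing/antimicrobial clothing based on chitosan or silver (intervention groups) at 12 months compared with baseline".
- Data collection, monitoring, and data analysis: "The data analysis will be conducted according to the intention-to-treat principle", and "The primary hypothesis is tested by means of linear mixed model analysis", with baseline EASI, group, continuous time and time by group.
- Cost-effectiveness: "QALYs will be measured for a 1-year period, based on the Dutch tariff for the EQ-5D". Cost data are requested weekly (Therapeutic clothing): "participants are requested to answer a weekly questionnaire on the use of therapy, AD symptoms, and costs".

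The Sample size section allows for 20% loss to follow-up without dividing it by cause. No section describes visits or questionnaires after rescue.

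**The concern.** Exit is triggered by the disease that the primary endpoint measures. If the clothing works, fewer active than control patients should need rescue, so the missing 12-month values would be unevenly spread and would belong to the patients doing worst.

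Two 12-month EASI differences then have to be kept apart. One is the no-rescue difference: what would be seen if nobody received UV or systemic treatment. The other is the intention-to-treat (treatment-policy) difference: what is seen in everyone as randomised, rescue included. The second suits a trial called pragmatic and needs EASI after rescue.

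The economic evaluation has the same gap. QALYs and questionnaire costs stop at rescue, when both are likely to change most, and a mixed model for EASI does nothing to restore them. An analysis plan can choose between the two differences only if the post-rescue data exist.

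**Working it through.** **The plan's own figure.** The article gives no rescue rate or size of bias to reproduce; its related figure is 55 per group. With SD 13, difference 6.6 (6.6/13 = 0.51), correlation 0.6 and the mean of four post-baseline visits, the variance factor is (1 + 3 × 0.6)/4 = 0.70. Then n = 2 × (1.96 + 0.84)² × 13² × 0.70 / 6.6² = 42.6, so 43, or 44 with the t distribution; 44/0.8 = 55. The 20% allowance enlarges N. It protects power and does not address why patients leave.

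**Inputs for the illustration.** From the Sample size section: SD 13, correlation 0.6, difference 6.6, visits at months 1, 3, 6 and 12. Assumed: control mean EASI 20; exit possible once EASI exceeds 35; rescue lowers EASI by r = 5, 10 or 20 points, lasting to month 12. The analysis is a random-intercept mixed model with the planned terms, read off at month 12. Two exit patterns were simulated:

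- A: exit at months 1, 3 or 6 with probability 0.5, EASI at the exit visit recorded.
- B: exit in any of months 1 to 11 with monthly probability 0.15, triggering EASI not recorded.

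**Formula.** Intention-to-treat difference = no-rescue difference − (control exits − active exits) × r.

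| | A | B |
|---|---|---|
| Exits, control vs active | 15.1% vs 6.2% | 15.5% vs 6.6% |
| No-rescue difference | 6.60 | 6.54 |
| Planned model | 6.59 | 6.29 |
| Intention-to-treat, r = 5 / 10 / 20 | 6.15 / 5.70 / 4.81 | 6.10 / 5.65 / 4.76 |
| Model minus intention-to-treat | 0.44 / 0.89 / 1.78 | 0.20 / 0.64 / 1.5 |
| Follow-up lost, control vs active | 11.4% vs 4.6% | 8.5% vs 3.5% |

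For A, 0.151 − 0.062 = 0.089 and 0.089 × 10 = 0.89, which matches. For B, 0.155 − 0.066 = 0.089 and 6.54 − 0.89 = 5.65; the model then exceeds this by 6.29 − 5.65 = 0.64.

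**Months lost per rescued control patient.** A: 0.114 × 12/0.151 = 9.1. B: 0.085 × 12/0.155 = 6.6. Pattern A allows no exit between months 6 and 12, which is why its loss is larger.

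**Model against the no-rescue difference.** In A they agree (6.59 vs 6.60). In B the model falls short by 6.54 − 6.29 = 0.25. A further simulation removed patients before the triggering visit (8,000 per arm, so the figures are rough). It gave 6.3 against 6.7 with about 12% vs 8% stopped, and 6.0 against 6.9 with 21% vs 14% stopped.

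**Sensitivity.**

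- No treatment effect: model minus intention-to-treat is near zero in both patterns (pattern A: exits 15.1% in each arm, model 0.00, intention-to-treat 0.01).
- True difference 3, pattern A: exits 15.2% vs 10.4%; model 3.02; intention-to-treat 2.79 / 2.55 / 2.07.
- Skewed EASI (gamma), pattern A: exits 15.0% vs 8.8%; model 6.57; intention-to-treat 6.30 / 5.97 / 5.31, so gaps of 0.27 / 0.60 / 1.26.
- Thresholds 30 to 45 and exit probabilities 0.25 to 1, at most 20% exits per arm, pattern A: gaps of 0.04–0.45 / 0.1–0.9 / 0.25–1.8.

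**The case against.** The strongest reply is that this is a choice of target. The mixed model uses all data up to exit, the no-rescue difference is a legitimate question, and the article treats UV and systemic immunosuppression as outside the regimen under study: both are barred in the month before inclusion and both end participation. EASI after rescue would partly reflect the rescue drug. This stands as far as it goes. It shows that the planned analysis has a meaning. It does not show that the other target, or a full year of QALYs and costs, remains available.

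Second, the size rests on assumptions. Rescue rate, threshold, control mean and duration of the rescue effect are not in the article, and the largest gaps need a 20-point fall held to month 12. This also stands, and is why ranges are given.

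Third, supporting statements should not be pressed too far. The Discussion says "Data concerning the use of topical corticosteroids, adherence to the clothing, and use of other therapy will be available for analysis"; data up to exit can satisfy that, so it is not contradicted. Nor does the Cost-effectiveness section say that costs come only from the questionnaire.

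Fourth, the full protocol, which is not shown, might provide for follow-up after exit. That is possible, but the sentence in the article says the opposite in plain terms.

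A reader might infer that the planned model necessarily overstates the effect. The article does not support so flat a claim. It does not say whether EASI is recorded at the rescue decision, and the last gap between visits is six months. If the flare is missed, the model can understate the no-rescue difference. In pattern B the excess over intention-to-treat would vanish if rescue lowered EASI by only 0.25/0.089 = 2.8 points.

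**Conclusion.** The point holds as a design weakness that should be fixed. As written, the protocol article ends data collection at rescue for patients whose measured disease has worsened. The intention-to-treat 12-month EASI difference and complete 1-year QALYs and questionnaire costs then cannot be obtained, and no analysis plan can recover them.

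Under assumed exits of about 15% control and 6% active, the planned model exceeds the intention-to-treat difference by roughly 0.2–0.4, 0.6–0.9 or 1.5–1.8 EASI points for a sustained rescue effect of 5, 10 or 20, against a target of 6.6. About 8–11% of control and 3–5% of active follow-up is lost, or about 6.5 to 9 months per rescued patient depending on when exit occurs. The true size is unknown because no rescue rate is given.

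Two stronger readings are not supported. The clause does not make an intention-to-treat analysis impossible to run: all randomised patients can enter the mixed model with data up to exit. It also does not create a false positive in these illustrations: with equal rescue rates and no effect, the bias is near zero. The harm is to the size and meaning of the estimate and to the economic evaluation.

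**What to change.** Keep the clinical rescue rule and stop the study clothing if needed, but do not end follow-up. For all who agree:

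- continue the scheduled blinded EASI visits and the EQ-5D and cost questionnaires to month 12;
- record the date and type of rescue, and an EASI at the rescue decision where feasible;
- use these data in the intention-to-treat and cost-effectiveness analyses, and keep the mixed model without post-rescue values as a sensitivity analysis for the no-rescue difference.

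The sample size does not change. The cost is one protocol amendment and a few dozen visits kept rather than cancelled. In pattern A, 17.9 visits per 55 control patients and 7.2 per 55 active patients remain after exit, so 17.9 + 2 × 7.2 = 32 with a true difference of 6.6, or 3 × 17.9 = 54 with no effect, out of 165 × 4 = 660 scheduled post-baseline visits. The downside is that EASI after rescue partly reflects the rescue drug and the reported difference may be smaller, which is why the no-rescue analysis should stay alongside.
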